**Figure 1 F1:**
[figure not shown]
Study design.

### Questionnaires and psychological tests

During the pre- and post-tests (on the inclusion and 12 months after the diagnosis), for the two groups (A « intervention » and B « control »), we use a battery of tests with a questionnaire and validated psychological tests.

The questionnaire covers the socio-demographic characteristics of the patients, their disease (objective and subjective criteria such as fatigue, anxiety, mood disorders…), changes in their socio-professional situation during the study, as well as the difficulties they encounter with regard to the repercussions of their cancer on their situation (sick leave, financial aid, employment, recognition of disability, psychological aid, paramedical assistance and guidance). Social fragility is estimated using the Epices score [35], which will enable the women who are the most fragile socially speaking (FS+) to be distinguished from those who are less fragile socially (FS-) through a cut-off at the median. The Epices score was in fact built on a questionnaire comprising the various dimensions of precariousness: nationality, level of education, occupation, composition of household, housing, social protection, perceived health, income, leisure activities, financial difficulties, social integration, seeking healthcare, serious events experienced before the age of 18 years.

The measurement of the social support is done by the QSSP [36], the coping strategies of the patient by the WCC [37], the attitude to problems by the QAP [38], anxiety and depression by the HADS scale [39] and the quality of life by the FACT-G [40]. The quality of the return to work is estimated by the assessment of the work ability (WAI) [41].

### Sample size

The number of patients was defined according to the expected reduction in the social inequalities of the return-to-work rate.

The research done by Quinton-Fantoni *et al. *[9] showed that the return-to-work rate 12 months after the diagnosis of women having had chemotherapy was 50% on average, but there was a difference of 22% between the most precarious and the least precarious cases.

The recruitment of 125 patients per group (A « intervention » and B « control »), with the acceptance of a first order risk of 5% and a power of 80%, would enable a reduction in the gap between the precarious cases and the non-precarious cases of 13.5 points to be demonstrated, enabling the difference in the return-to-work rate to be lowered from 22% to 8.5%. In order to make allowance for possible drop-outs during the study and unusable data, the minimum number of patients to be recruited was increased by 20%. The final number therefore comes to 150 women per group, i.e. a total of 300 patients.

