### Statistical analyses

The data will be entered twice then exploited in SAS V9.2 and SPSS v20. After the quality of the data has been checked and any corrections made, a description of the population included in the study will be given. A comparison of the main return-to-work criteria of the two groups drawn at random will be done (age, stage of development of the disease, occupational category).

The reduction in the social inequalities of the return to work will be studied by comparing the deltas (difference in the return-to-work rates between the two sub-groups FS + and FS-) between the control group « B » and the intervention group« A » having the benefit of the APAPI. A rough comparison of the two deltas will be done with a Chi2 test. The taking into account of adjustment factors (age, secondary effects of the treatment …) will be done with the aid of multivariate regression models.

As regards the secondary objectives, what is involved here is comparing for the 2 groups:

1) the deltas of the quality of the return to work at 18 and 24 months after the diagnosis (WAI and job retention rate); 2) the deltas of the psychosocial characteristics (QSSP, WCC, QAP, HADS and FACT-G scores) and the external resources (number of contacts with the SEIS platform) at 12 months from the diagnosis.

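### The 80% power claim does not hold for the planned comparison of gaps: with 125 women per group, power for a 13.5-point reduction is about 19%

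*Protocol article*

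**What the plan says.** The Sample size section of the protocol article takes from a cited study a 12-month return-to-work rate, after chemotherapy, that "was 50% on average, but there was a difference of 22% between the most precarious and the least precarious cases". It then states that 125 patients per group, at a first-order risk of 5% and 80% power, "would enable a reduction in the gap between the precarious cases and the non-precarious cases of 13.5 points to be demonstrated", so that the gap falls from 22% to 8.5%. The 125 is raised by 20% to 150 per group, 300 in total. No formula is named and the sidedness of the 5% is not given.

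Two other sections fix what is compared. Under Questionnaires and psychological tests, women are divided into more fragile (FS+) and less fragile (FS-) by the Epices score "through a cut-off at the median". Under Statistical analyses, the primary analysis consists of "comparing the deltas (difference in the return-to-work rates between the two sub-groups FS + and FS"-) between groups B and A. It adds: "A rough comparison of the two deltas will be done with a Chi2 test", with regression adjustment to follow.

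**The concern.** Each delta is a difference between two rates, and the trial compares one delta with another. This is a group-by-fragility interaction on the risk-difference scale. Its variance is the sum of four binomial variances, each from about half a randomised group. A calculation that takes each delta as the share of 125 women who have an event understates that variance severely.

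This is the primary objective, so the error bears on the trial's main conclusion. Readers who believe the study had 80% power could take a non-significant result as evidence that the support does not reduce inequality. The design would in fact leave the question open.

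**Working it through.** **Inputs.**
- From Sample size: 125 per group; alpha 0.05; power 0.80; gaps 0.22 (control) and 0.085 (intervention); average rate 0.50.
- From the median split: 125 / 2 = 62.5 women per cell.
- Assumed: a two-sided test, with one-sided shown alongside; equal halves, so that control rates are 0.50 ± 0.11 = 0.39 (FS+) and 0.61 (FS-). The intervention rates are not given. The main case is 0.525 / 0.61 (only FS+ improves); the alternative is 0.4575 / 0.5425 (average stays at 50%).

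**Step 1: reproduce 125.** Enter 0.22 and 0.085 as two independent proportions, with mean p̄ = 0.1525.

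n = [1.96·√(2·0.1525·0.8475) + 0.8416·√(0.22·0.78 + 0.085·0.915)]² / 0.135² = (0.9965 + 0.4203)² / 0.018225 = 110.1

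Continuity correction: (110.1 / 4)·[1 + √(1 + 4 / (110.1·0.135))]² = 124.5, rounded up to **125**.

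The other variants give 111 (two-sided, uncorrected), 107 (unpooled), 106 (arcsine), and 87 or 101 (one-sided, without and with the correction). Only the two-sided corrected form gives 125.

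**Step 2: standard error of the planned contrast.**

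SE = √[Σ p(1−p) / 62.5] = √[(3·0.39·0.61 + 0.525·0.475) / 62.5] = √(0.9631 / 62.5) = 0.1241

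The simple-proportion reading implies √[(0.1716 + 0.0778) / 125] = 0.0447. The true variance is therefore about 7.7 times the implied one (0.01541 / 0.00200).

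**Step 3: power.** 0.135 / 0.1241 = 1.088. Two-sided power = Φ(1.088 − 1.96) plus a negligible opposite tail = **0.193**.

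| Case | Two-sided | One-sided |
|---|---|---|
| 125 per group, only FS+ improves | 19.3% | 28.9% |
| 125 per group, average held at 50% | 19.1% | 28.7% |
| 125 per group, all cells at 50% variance | 18.7% | 28.2% |
| 150 per group, all evaluable, only FS+ improves | 22.2% | 32.5% |
| 125 read as the number per cell, average held at 50% | 33.4% | 45.5% |
| Extreme rates, 78/100% against 91.5/100%, 125 per group | 57.0% | 68.9% |

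The last row contradicts the stated 50% average and is shown only as a bound. Simulation with 400,000 replicates gives 19.3% to 19.4% two-sided for the first two rows; an interaction test on the logit scale gives 18.5% to 18.7%.

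**Step 4: what the size can deliver (two-sided, main case).**
- Gap removed entirely (intervention rates 0.61 / 0.61): SE = √(4·0.2379 / 62.5) = 0.1234; 0.22 / 0.1234 = 1.783; power about 43%.
- Reduction detectable with 80% power: (1.96 + 0.8416)·0.1241 = 0.348, about 35 points.
- 95% confidence interval half-width: 1.96·0.1241 = 0.243, about 24 points.
- Size for 80% power at 13.5 points: 0.9631·(2.8016)² / 0.018225 = 415 per cell, or 830 evaluable women per group (838 if the average stays at 50%).

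**The case against.** Several cautions are fair. The article names no formula, so the origin of 125 is an inference from an exact match. Sidedness is not stated; one-sided power is about 29%, and about 55% for complete removal of the gap. The 39% and 61% control rates need equal halves, and the cited study's definition of precariousness is not visible. The intervention rates are assumed, and the main case gives no benefit to FS- women although the Clinical prospects section expects some benefit for everyone. The chi-square comparison is described as rough, with adjusted models to follow. How a null result would be interpreted is not stated, and an article may leave such reporting rules to the full protocol or analysis plan.

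These points call for labelled assumptions but do not rescue the claim. The shortfall does not depend on how 125 was obtained. The cell-rate choices consistent with the article move two-sided power only between 18.7% and 19.3%. Covariate adjustment would have to cut the variance about 6.6-fold (415 / 62.5) to reach 80%; a 30% cut gives about 25%. Nor is this an omission that an unseen document could fill: the article prints a specific power figure that its own inputs contradict.

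**Conclusion.** The concern holds. With 125 evaluable women per group, the planned comparison has about 19% power two-sided (29% one-sided) for a fall in the gap from 22 to 8.5 points, against the 80% stated. At the two-sided 5% level the trial would more likely than not miss even complete removal of the gap. The reduction it could detect with 80% power, about 35 points, exceeds the 22-point gap it sets out to narrow.

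These figures are for the unadjusted contrast and rest on equal FS+ and FS- halves and the assumed intervention rates. No reading of 125 per group that agrees with the stated 50% average comes near 80%. The claim must be corrected.

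**What to change.** Correct the Sample size section and leave enrolment as it is:

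- Delete the 80% power statement.
- State that 125 evaluable women per group (about 62 per fragility cell) give about 19% power, two-sided 5% and unadjusted, for a reduction from 22 to 8.5 points, and 80% power only for about 35 points.
- State the expected 95% confidence interval for the difference in gaps, about ±24 points.
- State the sidedness and the four assumed cell rates behind these figures.

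The section should also say that the primary result will be reported as an estimate with its confidence interval, and that a non-significant test will not be taken to show that the gap is unchanged. This could equally stand in the analysis plan.

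The cost is a change of wording. No procedure, visit or patient number changes, but a published figure becomes much less favourable.

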### Data management

A dedicated database was created for the study which was tested out and validated before any data was entered. This dedicated database will be developed with the aid of Capture System (CLINSIGHT), which is a software package designed for the global management of clinical studies and meeting the study’s regulatory requirements. A data validation plan will be drawn up and will describe in detail the checks to be performed for each variable together with the list of the blatant errors for which correction is authorised.

The observation books will be checked when they are collected and then the data will be entered followed by post-checking (data entered/hard copy data). This data will be checked once again by the team in charge of the data management via the error messages received from the validation programmes. Blatant errors will be corrected. The other errors, omissions or inconsistencies will be mentioned on correction request forms that will be sent to the investigating physician and the corrections included in the database.

The database will be frozen after the final quality control then exported to the SPSS statistical software as per an automated and validated procedure.

### The participants

In the context of the study, two psychologists are responsible for doing the APAPI, each one reporting to an investigating site. In order to provide similar support from a theoretical and practical standpoint, and in accordance with the recommendations of Tamminga et al. [3] who stress the importance of individual intervention with a cognitive behavioural component, both the psychologists received prior training in cognitive behavioural therapy and work with an interview template specific to each meeting with the participants. Regular meetings will be held in order to harmonise their practices during the support provided.

The occupational physician of the occupational diseases and job retention unit of the Lille CHRU, a return-to-work specialist, is responsible for receiving each participant of the study following the 4 interviews with the psychologists. These consultations take place at the hospital department administering the standard care.

### Results expected

This is a multi-disciplinary project through which we hope the APAPI will enable a reduction in the social inequalities of the return to work (timescale, conditions, job retention rate) of the breast cancer patients compared with those who do not have the benefit of the APAPI.

The main observation we expect to make is that the social inequalities of the return-to-work rate 12 months after the diagnosis of the breast cancer patients are less for the APAPI group than for the control group.

We also expect to observe that this reduction in the inequalities in the intervention group compared with the control group also concerns the conditions and the return to work at 12, 18 and 24 months after the diagnosis, the psycho-social factors studied and worked on with the patients, that quality of life of the patients at 12, 18 and 24 months and the proportion of people having made use of the SEIS platform.

Another result expected is the overall improvement in all these factors in the intervention group compared with the control group.

### Statistical analyses

The data will be entered twice then exploited in SAS V9.2 and SPSS v20. After the quality of the data has been checked and any corrections made, a description of the population included in the study will be given. A comparison of the main return-to-work criteria of the two groups drawn at random will be done (age, stage of development of the disease, occupational category).

The reduction in the social inequalities of the return to work will be studied by comparing the deltas (difference in the return-to-work rates between the two sub-groups FS + and FS-) between the control group « B » and the intervention group« A » having the benefit of the APAPI. A rough comparison of the two deltas will be done with a Chi2 test. The taking into account of adjustment factors (age, secondary effects of the treatment …) will be done with the aid of multivariate regression models.

As regards the secondary objectives, what is involved here is comparing for the 2 groups:

1) the deltas of the quality of the return to work at 18 and 24 months after the diagnosis (WAI and job retention rate); 2) the deltas of the psychosocial characteristics (QSSP, WCC, QAP, HADS and FACT-G scores) and the external resources (number of contacts with the SEIS platform) at 12 months from the diagnosis.

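### The Chi2 comparison of the two deltas is not tied to a valid variance: if run as the trial was sized, it gives about 38% false positives; if run validly, it has about 19% power

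*Protocol article*

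**What the plan says.** Under Statistical analyses, the protocol article studies the reduction in social inequality by "comparing the deltas (difference in the return-to-work rates between the two sub-groups FS + and FS"-), control arm against intervention arm. The test named for this contrast is: "A rough comparison of the two deltas will be done with a Chi2 test". The next sentence adds: "The taking into account of adjustment factors (age, secondary effects of the treatment …) will be done with the aid of multivariate regression models". It names no arm-by-fragility term.

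Under Sample size, the planning inputs are:
- a 12-month return-to-work rate: "the return-to-work rate 12 months after the diagnosis of women having had chemotherapy was 50% on average";
- a gap by precariousness: "there was a difference of 22% between the most precarious and the least precarious cases";
- a target effect: "enabling the difference in the return-to-work rate to be lowered from 22% to 8.5"%;
- error rates: "with the acceptance of a first order risk of 5% and a power of 80"%;
- a number, later raised by 20% to 150 per group: "The recruitment of 125 patients per group (A « intervention » and B « control").

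Under Questionnaires and psychological tests, FS+ and FS- are separated at the median of the Epices score. Each arm of 125 therefore splits into subgroups of about 62 or 63.

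**The concern.** A Chi2 test in its usual form compares counts out of denominators. A delta is not a count. It is a difference of two rates, it can be negative, and its variance is the sum of two binomial variances, each on half an arm. The analysis sentence gives no denominator, variance or degrees of freedom, so the reader has to look elsewhere for what is meant. The only other guide in the article is the sample-size calculation, and that points to the invalid version, in which 22% and 8.5% are handled as two ordinary proportions on 125 women each.

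This contrast carries the main objective. If it is tested with a standard error less than half the true one, chance differences between the two gaps would often be reported as the intervention narrowing, or widening, social inequality in return to work.

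**Working it through.** **Inputs.** From the article: mean rate 50%; control gap 22 points; target gap 8.5 points (difference 13.5); alpha 5%; power 80%; 125 evaluable per arm; median split. Assumed: two-sided alpha (sidedness is not stated), equal FS+ and FS- halves, and subgroup rates of 50 ± 11 = 39% (FS+) and 61% (FS-).

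**1. Reproducing 125.** Treat the deltas as single proportions, p₁ = 0.22 and p₂ = 0.085, with mean 0.1525 and d = 0.135.

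- Uncorrected: n₀ = [1.96·√(2 × 0.1525 × 0.8475) + 0.8416·√(0.22 × 0.78 + 0.085 × 0.915)]² / 0.135² = (0.9965 + 0.4203)² / 0.018225 = 110.1, i.e. 111.
- Continuity-corrected: n = (n₀/4)·[1 + √(1 + 4/(n₀d))]² = 27.53 × (1 + 1.1265)² = 124.5, i.e. **125**, the stated figure.

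The other variants tried do not match: 111 two-sided uncorrected, 107 with unpooled variance, 106 with the arcsine transformation, and 87 one-sided (101 with correction). Also 125 × 1.2 = 150, as stated.

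**2. Standard error of the difference of deltas when both true gaps are 22 points.**

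- As sized: √(2 × 0.22 × 0.78 / 125) = 0.0524, about 5.2 points.
- From all four cells: √(4 × 0.39 × 0.61 / 62.5) = 0.1234, about 12.3 points.
- Ratio: 0.1234 / 0.0524 = 2.35.

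**3. False-positive rate if the test is run as sized (125 per arm).**

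- Without continuity correction, the test rejects when the deltas differ by more than 1.96 × 5.24 = 10.3 points. Then 10.3 / 12.34 = 0.832, and 2[1 − Φ(0.832)] = 40.5%.
- With the correction, the threshold rises by 1/125 = 0.8 points to 11.1. Then 11.1 / 12.34 = 0.897, and 2[1 − Φ(0.897)] = 37%.
- With the correct standard error, the threshold would be 1.96 × 12.34 = 24.2 points.

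Simulation (400,000 trials, 39% and 61% in both arms) gives about 41 to 42% without the correction and 37 to 38% with it. The spread reflects how negative deltas are handled. At 150 per arm the figures are about 41% and 37 to 38%. Rejections that favour the intervention make up about half, 18 to 21% of all such trials.

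**4. The valid chi-square.** A 1-df Wald chi-square on the difference of the deltas, with all four cell variances, rejects in 5.3% of the same null trials. Its power for 22 against 8.5 points, taking 39/61 in control and 45.75/54.25 in intervention, is:

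- SE = √[(2 × 0.39 × 0.61 + 2 × 0.4575 × 0.5425) / 62.5] = 0.1247.
- Power at 125 per arm = Φ(0.135 / 0.1247 − 1.96) = Φ(−0.88) = **19%** (simulation 19.2%). At 150 per arm it is 22%. With a one-sided 5% test it is 29% at 125.
- For 80% power, two-sided, n per subgroup = (1.96 + 0.8416)² × 0.9722 / 0.135² ≈ 419, about 837 evaluable per arm. Other ways of reaching an 8.5-point gap give 820 to 830.
- The reduction detectable with 80% power at 125 per arm is 2.8016 × 0.1247 = 34.9 points, more than the whole 22-point gap.

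**The case against.** The best defence is that a chi-square test need not be the naive one. A 1-df Wald or heterogeneity chi-square on the difference of the two deltas is a Chi2 test, is valid, and fits the sentence as written. This stands. A reader might infer that no Chi2 test could be right here, and the article does not support that. What it supports is that the sentence does not identify the valid test, while the sizing points to an invalid one. Under the valid reading, the stated 80% power fails.

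Second, a sample-size shortcut does not bind the analysis, and the naive test is awkward to run: 22% of 125 is 27.5 women, and no patient-level variable has a delta as its rate. This also stands, and it is why the 38% is conditional. A reader might infer that the trial will have a false-positive rate near 40%, but the article does not establish which test would be run.

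Third, the article calls the comparison rough and follows it with regression. That does not settle the matter. An unadjusted test should also hold its level, and the regression is described only as handling adjustment factors. A reader might go further and infer that the adjusted model tests odds ratios rather than the gap in points. The article states no link function, so that is not claimed, and the choice can properly sit in the full protocol or SAP. Nor does the article propose any other misuse of Chi2, such as one test across all four cells or separate tests by arm.

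**Conclusion.** The point holds in conditional form. As written, the analysis sentence and the sample-size calculation are compatible only under an invalid test. Either the analysis follows the sizing, with a type I error of about 38% (37 to 42% depending on continuity correction, 125 or 150 per arm, and handling of negative deltas), or it uses a valid 1-df contrast, with about 19% power in place of the stated 80%.

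These figures rest on two-sided testing, equal halves at the median split, and 39% and 61% derived from the 50% mean and the 22-point gap. They are not sensitive to the overall level: raising both rates in one arm by 10 points leaves the naive error at about 37 to 41%. Only about half of the false rejections would be claims of benefit. This goes beyond detail left to a SAP, because the article itself names the test and sizes the trial in a way that points to the wrong variance.

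**What to change.** Replace the Chi2 sentence with wording along these lines: the unadjusted comparison is a 1-df test of the arm-by-fragility contrast on the risk-difference scale, with variance from all four cells (for example a Wald chi-square), and the difference of the two deltas is reported with its 95% CI. State that the adjusted model estimates the same contrast; several standard methods do this.

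Then restate the power under Sample size for that test, including whether alpha is one- or two-sided. On the article's own inputs this is about 19% at 125 per arm and 22% at 150, against about 820 to 840 evaluable per arm for 80%. The sponsor can then decide whether to change the number or to present the contrast with its confidence interval as an estimate of limited precision.

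The change to the test is wording only. It needs no new data and can be done in the SAS and SPSS already named. Restating the power costs nothing to compute; only a decision to enlarge the trial would carry a real cost.

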### Care and randomisation of patients

The standard care for breast cancer patients at each site is the same: following the cancer diagnosis, the medical files of the patients are examined at a multidisciplinary coordination meeting the purpose of which is to decide on the course of treatment to be given. Within a timescale of 1 to 2 weeks from the diagnosis, the patients are seen by an oncologist who explains to them what their course of medical treatment will consist of and whether or not this will involve chemotherapy. An appointment is then made for the following week with a nurse for a pre-chemotherapy consultation. During this interview lasting approximately 90 minutes, the nurse reviews with the patient what she has understood about the diagnosis and the treatment and her concerns and needs. The nurse can direct the patient to other professionals (psychologist, dietician, physiotherapist, welfare worker). The first chemotherapy session takes place approximately 1 month after this consultation.

The study is therefore proposed by the medical oncologist during the first care consultation to the patients fulfilling the inclusion criteria in the 2 investigating centres. After having explained the study to the patients with the information leaflet, those who accept sign a consent form. Next the patients will be randomised into two groups: 1) Group A: the « intervention » group which will have the benefit of the early active individualised psychosocial support in addition to the usual care. 2) Group B: the «standard care » group hereafter referred to as the “control group” which will follow the regular course of treatment without having the benefit of the psychosocial support as described above. This standard care already includes tools for identifying situations of great social distress enabling the patients to be directed to the regular social helpers.

Just after the inclusion, and before the start of their chemotherapy treatment, both groups of patients undergo the same battery of tests (pre-test).

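### The adjusted comparison of the return-to-work deltas conditions on treatment side effects, which largely arise after randomisation and may be changed by the support

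*Protocol article*

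**What the plan says.** Under Statistical analyses, the reduction in social inequality is studied as the FS+/FS- difference in return-to-work rate, compared between the intervention and control groups. Two steps are given. The first is unadjusted: "A rough comparison of the two deltas will be done with a Chi2 test". The second is adjusted: regression models are to take account of "adjustment factors (age, secondary effects of the treatment", with the list left open after these two. Side effects are thus one of only two adjustment factors named, and nothing limits them to a value taken at baseline.

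The timing is in Care and randomisation of patients. "The study is therefore proposed by the medical oncologist during the first care consultation"; consent follows, and then "Next the patients will be randomised into two groups". Chemotherapy starts later. Under Meetings with the psychologist, the first interview falls on the day of the first chemotherapy session, the second and third on the sixth and final sessions, and the fourth three months after radiotherapy ends.

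**The concern.** A covariate measured after allocation is safe in a model for a treatment effect only if the treatment cannot change it. Here the protocol's own text supports both links of a causal path.

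- **Support to symptoms.** The interviews work on coping and problem solving and may include relaxation. Anxiety, depression and quality of life are secondary outcomes that the trial hopes to improve. Women know whether they are receiving interviews, so symptom reporting may also differ by arm.
- **Symptoms to return to work.** Factors associated with the return to work lists freedom from pain, fatigue and mental co-morbidity among the factors that favour return.

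Clinical prospects expects everyone to benefit but fragile women to benefit more. A path through side effects could therefore act on the contrast of interest itself, and the regression would remove that part of the effect. Medico-economic analyses also takes its effect on regaining employment from the statistical model. If the adjusted model is meant, the problem carries over to the cost-benefit result.

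**Working it through.** **Planned effect.** Sample size gives a gap of 22 points falling to 8.5, so the target difference in deltas is 22 − 8.5 = 13.5 points.

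**Order of events from the documents.** First oncology consultation and consent, then randomisation, then the first chemotherapy session with the first support interview on the same day, then later sessions and interviews in parallel, then radiotherapy where given. Side effects of chemotherapy and radiotherapy follow allocation. Sequelae of surgery need not, because Participants requires surgery before the adjuvant chemotherapy.

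**Effect of conditioning (linear probability model with an arm-by-fragility interaction).** Let

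- T = true difference in deltas, 13.5 points (Sample size);
- c = drop in return to work caused by a side effect, 0.25 (assumption);
- r₊ and r₋ = points by which the support lowers side-effect prevalence in FS+ and FS- (assumptions).

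The part of T that runs through side effects is c × (r₊ − r₋). Conditioning on side effects removes it:

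adjusted difference = T − c × (r₊ − r₋)

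| r₊ | r₋ | Calculation | Adjusted estimate (points) |
|---|---|---|---|
| 0 | 0 | 13.5 − 0.25 × 0 | 13.5 |
| 10 | 0 | 13.5 − 0.25 × 10 | 11.0 |
| 20 | 0 | 13.5 − 0.25 × 20 | 8.5 |
| 30 | 0 | 13.5 − 0.25 × 30 | 6.0 |
| 20 | 20 | 13.5 − 0.25 × 0 | 13.5 |
| 20 | 10 | 13.5 − 0.25 × 10 | 11.0 |
| 10 | 20 | 13.5 + 0.25 × 10 | 16.0 |

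A large-sample simulation with 50% side-effect prevalence (assumption) agrees with these values. The model without the covariate returns 13.5 in every row, apart from simulation error.

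**Adding an unmeasured shared cause.** Assume a binary factor, present in half the women, that raises side effects by 40 points and lowers return to work by 20. Its variance is 0.25, so its covariance with side effects is 0.40 × 0.25 = 0.10. The variance of side effects is about 0.25. The fitted coefficient then grows from 0.25 to about 0.25 + 0.20 × 0.10 / 0.25 = 0.33. With r₋ = 0 and r₊ = 10 or 20, the estimate is 13.5 − 3.3 = 10.2 or 13.5 − 6.6 = 6.9. At r₊ = 30 the simulation gives 3.4, slightly below the 3.6 from the formula, because side effects vary less in that cell. With equal reductions in both strata the shared cause adds no bias to this contrast.

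**Effect of the support within a stratum.** Equal reductions cancel only in the difference. With r = 20 in both strata, the adjusted arm effect in each stratum is lower by 0.25 × 20 = 5 points. That matters if the economic analysis uses the adjusted model.

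**The case against.** Several stronger readings are tempting, and the documents do not support them.

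- **That the primary analysis is biased.** No model is labelled primary. The crude comparison of deltas contains no covariate and is untouched. Calling it rough may suggest that the regression is the one to rely on, but the word may equally mean unadjusted.
- **That bias is certain and pulls the effect down.** In a linear model the difference in deltas moves only if the support changes side effects differently by fragility. It can also move upwards, as the last table row shows. The FS+-only rows are stronger than the protocol's own expectation, which is benefit for all and more for fragile women.
- **That every side effect is post-randomisation.** Surgical sequelae present at inclusion could be legitimate baseline covariates.
- **That the covariate is self-reported fatigue or mood.** The questionnaire records "objective and subjective criteria such as fatigue, anxiety, mood disorders", but as features of the disease. The adjustment factor is not defined and could be clinically recorded toxicity, which psychological support is less likely to change.

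All four points stand and limit the claim. It can also be said that the list is illustrative and stands in a condensed article, and that side effects predict return to work. Neither answers the point. The item is named, not left out, and prognostic value does not justify conditioning on a post-allocation variable when the total effect of the support is wanted.

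**Conclusion.** The concern holds in a limited form. The protocol names an adjustment factor that, for chemotherapy and radiotherapy, arises after allocation and while the support is being delivered. A regression that includes it does not in general estimate the total randomised effect of the support. For the difference in deltas, bias requires a differential effect on side effects by fragility. The protocol makes this plausible without giving its size or sign. Under the assumed 25-point penalty, differences of 10 to 30 points in favour of FS+ reduce 13.5 points to between 11.0 and 6.0, or to between 10.2 and 3.4 with the assumed shared cause. No differential effect means no bias, and a larger reduction in FS- reverses the sign. These figures show how the estimate responds to the assumptions; they do not predict what will happen in this trial. The exact cancellation under equal reductions is a property of the linear model and should not be relied on if a logistic model is fitted.

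**What to change.** In Statistical analyses, remove treatment side effects arising after randomisation from the adjustment set of the regression for the return-to-work deltas. Adjust only for variables fixed at randomisation: centre, age, disease stage and occupational category.

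Pre-test scores need care. The protocol describes randomisation first and then says that "before the start of their chemotherapy treatment, both groups of patients undergo the same battery of tests", so it does not show that scores completed before allocation exist. Use these scores only if they were completed before allocation; otherwise state that they were collected after allocation but before the first interview.

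Report side effects by arm, or in a mediation analysis labelled as such. State that the effect passed to the economic analysis comes from a model without post-randomisation covariates.

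The cost is a few lines of wording, settled before analysis, and no new data. The downside is the loss of some prognostic adjustment.
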